To improve the ORR and resection rate of liver metastases, researchers have tried to use more active treatment regimens, such as FOLFOXIRI triplet regimen consisting of 5-FU/CF, L-OHP, and CPT-11, or combination of targeted drugs with a chemotherapy backbone such as bevacizumab targeting vascular endothelial growth factor (VEGF) and cetuximab targeting epidermal growth factor receptor (EGFR). In the observational phase Ⅳ study First BEAT, among 704 patients with initially unresectable metastatic colorectal cancer (mCRC) whose metastases were confined to the liver, 84 patients (11.9%) underwent curative resection of liver metastases after treatment with bevacizumab plus first-line chemotherapy, of which 69 patients (9.8%) achieved R0 resection [3]. However, the study by Saltz LB et al. analyzed the efficacy of first-line bevacizumab plus FOLFOX/XELOX versus FOLFOX/XELOX regimen alone in 1400 patients with advanced CRC, and the results showed that the combination of bevacizumab did not significantly improve the ORR or tumor regression [4]. The results of two studies of FOLFOXIRI triplet regimen, GONO and HORG, showed that FOLFOXIRI triplet regimen could improve the ORR and R0 resection rate of metastases compared with FOLFIRI doublet regimen. In the GONO study, the overall ORR increased from 41% for the doublet regimen to 66% for triplet regimen; P = 0.0002; the R0 resection rate was 15% vs. 6%, respectively (P = 0.033); in the HORG study, the overall ORR increased from 33.6% for doublet regimen to 43% for triplet regimen, P = 0.168; and the R0 resection rate was 10% vs. 4%, respectively (P = 0.008) [5]. The results of GONO study showed that compared with doublet regimen, FOLFOXIRI triplet regimen could achieve longer median overall survival (OS) (23.4 months vs. 16.7 months, P = 0.026). However, the toxicity and adverse events of triplet chemotherapy were significantly increased compared with the standard doublet regimen, especially hematological toxicity and peripheral neurotoxicity, which reduced the tolerance and compliance of patients [6].

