**5. Study regimen**

### 5.1 Study steps and procedures

1. The screening procedure begins after the patients sign the written informed consent.
2. CT and/or MRI scans (with PET-CT where available) are used to assess liver metastases and to exclude extrahepatic metastases.
3. An MDT meeting is held prior to chemotherapy and the resectability of metastases is assessed and determined based on the given criteria. The liver surgeon performs a comprehensive assessment of each patient’s baseline liver metastases, record in detail the number and size of liver metastases, the liver segment involved, whether the hepatic vein, portal vein, and inferior vena cava are involved, and explain in detail why each patient is considered initially unresectable.
4. Eligible patients at screening are randomly assigned by the study physician to receive either cetuximab plus FOLFOXIRI triplet regimen or cetuximab plus FOLFOX doublet regimen.
5. CT and/or MRI scans are performed every 4 cycles after chemotherapy, with additional examinations if necessary, and the tumor is assessed according to RECIST v1.1 criteria; MDT discussion is held regularly to determine the resectability of patients’ liver metastases. The reason why each patient can be converted to surgically resectable is also specified.
6. In this study, 8 courses (no less than 6 courses) of conversion chemotherapy are recommended, and some patients also need to appropriately prolong the treatment course. This is mainly because that this study includes patients with unresectable colorectal liver metastases, who usually have a large number of liver metastases, large lesions, with high-risk CRS score. Current clinical practice recommends surgical resection after adequate chemotherapy to achieve more benefit.

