**Cetuximab + mFOLFOXIRI regimen**

Cetuximab 500 mg/m^2^ ivd 90 min d1

Irinotecan 130 mg/m2 ivd d1 (The starting dose of irinotecan is 130 mg/m2, according to the “3 + 3” design. If 0/3 patients experience dose limiting toxicity (DLT), the dose should be increased to 150 mg/m2; if 1/3 patients experiences DLT, the number of enrolled patients should be increased to 6; if ≤ 1/6 patients experience DLT, the dose should be increased to 150 mg/m2; if ≥ 2/6 patients experience DLT, the dose of irinotecan should be decreased to 100 mg/m2.

At the dose of 150 mg/m2, if 0/3 patients experience DLT, the dose is determined to be 150 mg/m2; if 1/3 patients experiences DLT, the number of enrolled patients should be increased to 6; if ≤ 1/6 patients experience DLT, the dose is determined to be 150 mg/m2; and if ≥ 2/6 experience DLT, the dose is determined to be 130 mg/m2). UGT gene detection is recommended. For patients with UGT*28 7/7, UGT*6 A/A, UGT*28 6/7 and UGT*6 A/G, irinotecan at the dose of 130 mg/m2 is used, no need for escalation)

Oxaliplatin 85 mg/m^2^ ivd 3h d1

L-leucovorin 200 mg/m^2^ ivd d1 (d,l-leucovorin 400 mg/m^2^)

5-FU 2400 mg/m^2^ ivd civ 46h d1

The above regimen is repeated every 14 days.

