**6. Chemotherapy dose adjustment and concomitant medication**

**6.1 Overview**

Toxicities will be assessed according to NCI CTCAE v4.03 criteria starting from the first treatment cycle and will need to be repeated prior to and at the end of each subsequent treatment cycle. The following are general considerations for dose modifications due to chemotherapy-related adverse reactions:

- Dose reductions or interruptions may not be required if, at the discretion of the investigator, the adverse reaction is unlikely to develop into a serious or life-threatening event and will not result in treatment delay or interruption (e.g., alopecia, taste alteration, etc.). If anemia can resolve well with transfusion, no dose reduction or treatment interruption is required.
- If any Grade 1 adverse reactions occur, treatment may be continued at the starting dose without dose interruption.
- Prior to each new treatment cycle, patients should meet the following criteria:

Normal hematologic function (platelets > 90 × 10^9^/L; leukocytes > 3 × 10^9^/L; neutrophils > 1.5 × 10^9^/L).

Serum bilirubin ≤ 1.5 times ULN and transaminases ≤ 5 times ULN.

Serum creatinine < ULN, or calculated creatinine clearance > 50 ml/min (using the Cockcroft-Gault formula).

Recovery to baseline or ≤ Grade 1 from any treatment-related Grade 3/4 non-hematologic adverse reactions (except alopecia).

- If the patient is ineligible for FOLFOXIRI or FOLFOX chemotherapy, treatment with cetuximab or FU/CF chemotherapy can be continued. If the patient is ineligible for cetuximab treatment, FOLFOXIRI or FOLFOX chemotherapy can be continued.

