**6.5 Management of other toxicities**

If other Grade < 3 toxicities not listed above occur, give symptomatic treatment whenever possible. If Grade 3 toxicity occurs, withhold the drug treatment. When the toxicity recovers from Grade 3 to Grade ≤ 1, administer the corresponding investigational drug at 85% of the original dose in the next treatment cycle. If Grade 4 toxicity occurs, discontinue all drug treatment. If the toxicity still does not resolve to Grade ≤ 1 four weeks after the start of the next scheduled cycle, the patient should withdraw from the treatment and be followed up according to the protocol until the toxicity is resolved.

However, in the event of certain Grade ≥ 3 adverse events (e.g., when a patient develops symptoms of fatigue, sexual function changes, and clinically insignificant dry skin), the investigator may also decide to allow the patient to continue treatment.

For the second occurrence of non-hematological toxicity, the following dose adjustment methods should be used:

If the patient experiences Grade 3 toxicity again, although the dose of the investigational drug has been previously adjusted, the study dose can still be adjusted again if the investigator believes that the treatment is in the best interest of the patient (otherwise the treatment should be stopped). Adjust the second dose to 70% of the original dose. However, for the second occurrence of Grade 4 toxicity, the above principles do not apply, and the patient should discontinue treatment in this case. If the dose has already been reduced, it cannot be increased thereafter.

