## 9. Assessment during the study

## 9.1 Pre-chemotherapy assessment

The following assessments will be performed during each course:

- Concomitant medication
- Clinical data: weight, physical examination, vital signs, ECOG performance score
- Laboratory tests: hematology, biochemistry (including ALP) and tumor markers on Day 0 and Day 14
- EKG
- Tumor assessment:

Assessments will be performed every 4 courses and the number of examinations may be increased if necessary.

Tumor measurements/assessments are performed using CT or MRI scans based on RECIST v1.1 criteria.

For each patient, the same assessment method should be used throughout the study, and the assessment should be performed by the same assessor as far as possible.

All metastases detected at baseline screening should be assessed at every tumor assessment.

- MDT assessment:

Every 4 courses, the number of assessments may be increased if necessary.

In this study, 8 (no less than 6) courses of conversion chemotherapy are recommended, and some patients also need to appropriately prolong the treatment course before hepatectomy with or without radiofrequency treatment is considered.

This is mainly because that this study includes patients with unresectable colorectal liver metastases, who usually have a large number of liver metastases, large lesions, with high-risk CRS score. Current clinical practice recommends surgical resection after adequate chemotherapy to achieve more benefit.

- Chemotherapy related adverse events
- Survival

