**2.5. Frequency of tumor re-evaluation**

Frequency of tumor re-evaluation while on treatment should be protocol specific and adapted to the type and schedule of treatment. However, in the context of phase II studies where the beneficial effect of therapy is not known, follow-up every 6–8 weeks (timed to coincide with the end of a cycle) is reasonable. Smaller or greater time intervals than these could be justified in specific regimens or circumstances. The protocol should specify which organ sites are to be evaluated at baseline (usually those most likely to be involved with metastatic disease for the tumor type under study) and how often evaluations are repeated. Normally, all target and non-target sites are evaluated at each assessment. In selected circum- stances certain non-target organs may be evaluated less frequently. For example, bone scans may need to be repeated only when complete response is identified in target disease or when progression in bone is suspected.

After the end of the treatment, the need for repetitive tumor evaluations depends on whether the trial has as a goal the response rate or the time to an event (progression/death). If ‘time to an event’ (e.g., time to progression, disease-free survival, progression-free survival) is the main end-point of the study, then routinely scheduled re-evaluation of protocol-specified sites of disease is warranted. In randomized comparative trials in particular, the scheduled assessments should be performed as identified on a calendar schedule (for example: every 6–8 weeks on treatment or every 3–4 months after treatment) and should not be affected by delays in therapy, drug holidays or any other events that might lead to imbalance in a treatment arm in the timing of disease assessment.

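### On-treatment scans follow courses given rather than the calendar, so unequal treatment delays could make ETS and PFS be read at different times in the two arms

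*Protocol*

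**What the plan says.** Protocol Section 5.1 states that "CT and/or MRI scans are performed every 4 cycles after chemotherapy", and Section 9.1 that "Assessments will be performed every 4 courses and the number of examinations may be increased if necessary". Neither gives a week number or a window.

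The nominal course length is in Section 5.2: "The above regimen is repeated every 14 days". That line stands under the triplet regimen. I read it as covering both arms, which fits the flowchart's 3 to 4 months for 6 to 8 courses.

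Courses are conditional. Section 6.1 says "Prior to each new treatment cycle, patients should meet the following criteria", and lists blood count, liver, renal and toxicity recovery limits. Section 6.5 contemplates long holds for toxicities not listed elsewhere: "If the toxicity still does not resolve to Grade ≤ 1 four weeks after the start of the next scheduled cycle", the patient leaves treatment.

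Section 7.1 reads ETS after four courses, but measures PFS in calendar time from the start of study treatment. After treatment ends, Section 9.3 sets imaging every 3 months in both arms.

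Appendix IV, 2.5, says of randomised comparative trials that "the scheduled assessments should be performed as identified on a calendar schedule" and that these assessments "should not be affected by delays in therapy, drug holidays or any other events that might lead to imbalance in a treatment arm". Section 1 reports that "the toxicity and adverse events of triplet chemotherapy were significantly increased compared with the standard doublet regimen".

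**The concern.** The scan clock runs on courses delivered, and courses are held for toxicity. If one arm is held more often, its scans come later in calendar time. Two secondary endpoints inherit this. ETS is meant to be an early reading, yet it would be taken at different weeks in the two arms. Progression is dated at the scan that finds it, so PFS would be recorded on different grids.

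An analysis plan cannot repair this afterwards, because it cannot supply images that were never taken at comparable times. The allowance for extra scans is discretionary, in an open-label trial with investigator assessment, and does not align the arms. The protocol also departs here from the response criteria that it reproduces as its own appendix.

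**Working it through.** **The plan's own figures.** The protocol states no delay rate, ETS rate or PFS effect. Its planning figure is 128 patients for response rate (80% vs 60%, two-sided 10%, power 80%). With pooled variance, n per arm = [1.645·√(2·0.7·0.3) + 0.842·√(0.8·0.2 + 0.6·0.4)]² / 0.2² = 63.9, so 64 per arm and 128 in total. This agrees with the protocol and does not depend on scan timing.

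**Scan timing.** With no delay, scan k falls at 4k × 2 weeks: weeks 8, 16 and 24 for courses 4, 8 and 12 (12 is the maximum). With a mean delay of d weeks per course it falls at 4k(2 + d):

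| d (assumed) | Scan 1 | Scan 2 | Scan 3 |
|---|---|---|---|
| 0 | 8 | 16 | 24 |
| 0.25 | 9 | 18 | 27 |
| 0.5 | 10 | 20 | 30 |
| 1 | 12 | 24 | 36 |

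One hold of the four weeks named in Section 6.5 would alone move the first scan from week 8 to week 12.

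**PFS with no true difference.** All of the following are assumptions:
- Exponential PFS, identical in both arms, with median 9.5 months (the only PFS figure for cetuximab plus triplet in Section 1), 12 or 15 months.
- Scans after courses 4, 8 and 12, then every 13 weeks, each with ±1 week jitter.
- Each course slips one week with probability 0.1 in the doublet arm and 0.35, 0.6 or 1.0 in the triplet arm. Mean first scan is at 8 + 4p: week 8.4, against 9.4, 10.4 or 12.0.
- Every patient is followed to progression.

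| Triplet slip probability | Extra detection lag, progressions before week 26 (weeks) | Spurious HR to week 26 | Spurious HR, full follow-up |
|---|---|---|---|
| 0.35 | about 0.5 | about 0.85 | 0.96 to 0.97 |
| 0.6 | 1.1 to 1.2 | 0.88 to 0.89 | 0.98 to 0.99 |
| 1.0 | about 1.9 | about 1.02 | 1.02 to 1.04 |

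At 70 per arm, the chance of a log-rank z below −1.645 in the triplet's favour is 3% to 8%, against 5% to 6% when delays are equal. With scans fixed at weeks 8, 16 and 24 in both arms, the hazard ratio is 0.99 to 1.02 to week 26 and 0.99 to 1.01 overall, so the artefact goes.

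**ETS.** Assume that log size change at week 8 is normal with SD 0.35 and mean μ, with μ set so that P(shrinkage ≥ 20%) is 60%, 70% or 80%. For a reading at week w there are three cases:
- Shrinkage continues with time: Φ[(ln 0.8 − μw/8)/(0.35w/8)]. ETS rises 2 to 3 points at week 9, 3 to 5 at week 10 and 5 to 8 at week 12.
- Shrinkage follows doses given: no change, since both arms have had four courses.
- Tumour regrows 3% a week during the delay: Φ[(ln 0.8 − μ − 0.03(w − 8))/0.35]. ETS falls 2 to 3, 5 to 7 and 11 to 14 points.

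The protocol does not say which case applies.

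**The case against.** A reader might infer that later scans flatter the triplet on both endpoints. The documents do not support that.
- For PFS, a single landmark placed between the two arms' scans can show the delayed arm ahead, but the sign depends on the week chosen. Take grids 8/16/24 and 9/18/27, then every 13 weeks, with a 52-week median in both arms. Recorded PFS at week t is 2^(−s/52), where s is the last scan by week t. At week 20 this gives 80.8% (s = 16) for the undelayed arm and 78.7% (s = 18) for the delayed one; at week 30, 72.6% (s = 24) and 69.8% (s = 27). Over the first 52 weeks the delayed arm is ahead for 11 and behind for 33, and the restricted-mean difference is 0.11 weeks. The protocol plans a stratified log-rank test over the whole curve, not a landmark.
- For ETS, a benefit requires tumours to go on shrinking while treatment is withheld. Nothing in the protocol says so.

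Other objections are partly sound:
- Appendix IV says should, not must. Its calendar sentence follows a remark about trials whose main endpoint is time to event, whereas here it is response rate. The same section finds 6–8 weekly scans timed to the end of a cycle reasonable in phase II, and four 14-day courses are nominally 8 weeks. So the interval is acceptable. But the calendar advice names randomised comparisons in particular and its example includes on-treatment scans, so it is not confined to follow-up.
- The toxicity statement follows trials of triplet chemotherapy against an irinotecan doublet, not against cetuximab plus FOLFOX, and the study triplet omits the 5-FU bolus given in the doublet. More delay on the triplet is plausible, but its size is not documented.
- Post-treatment imaging is already 3-monthly in both arms, which limits the exposure to at most 12 courses. The simulation also leaves out surgery and the assessment before adjuvant treatment.

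**Conclusion.** The point holds as a scheduling weakness, not as a demonstrated bias in favour of either arm. Sections 5.1 and 9.1 let treatment delays move the endpoint scans, against the advice in the protocol's own Appendix IV. Unequal delays are foreseeable from Section 1 but not quantified there.

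The effect on PFS over full follow-up is probably small: a spurious hazard ratio within about 4% of 1 in either direction under the delays tried. Early PFS is more exposed, with ratios near 0.85 to 0.89 under moderate delays but none of that under the heaviest. ETS could shift by a few points up or down, or not at all. These sizes rest on assumed delay rates, PFS medians above 9.5 months, ETS rates and tumour behaviour during a hold. Response rate as a best response is less exposed, and the sample size is unaffected. This is a cheap improvement to secondary endpoints, not a threat to the primary comparison.

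**What to change.** In Sections 5.1 and 9.1, set endpoint scans in both arms at fixed weeks from the time origin used for PFS. That is the start of study treatment as Section 7.1 now has it, or randomisation if that origin is changed. Use the interval already implied, every 8 weeks on treatment (4 × 14 days) with a ±1 week window, whatever the course delays. In Section 7.1, read ETS at the week-8 scan. Multidisciplinary resectability reviews may still follow courses.

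The cost is wording in three sections. A delayed patient may be scanned mid-course, or occasionally once more before surgery. No treatment rule changes.

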**9.2 Surgery and related assessments**

Surgery data is recorded in the designated section of the CRF form and include surgeon name, surgery type, duration, ischemic time, type of blood product transfused, and hospitalization time.

Surgical complications are assessed at 48 hours, 1 month, and 3 months after surgery. Assessment indicators include perioperative mortality (within 60 days after surgery), intraoperative bleeding/transfusion, postoperative transfusion, systemic complications, and local liver complications. Systemic complications are defined as: pulmonary complications, cardiovascular complications, urethral complications, infections, wound healing, and iatrogenic complications. Local liver complications include bile leakage, bleeding, infectious perihepatic fluid collection, and liver dysfunction. The assessment criteria of Clavien-Dindo grading scale system is used. Resected metastases are examined pathologically to determine if they are completely resected.

**9.3 Post-treatment follow-up**

Patients who have completed the treatment specified in the protocol or have not completed the treatment due to intolerable adverse reactions, but have not experienced tumor progression, are followed up every 3 months, including physical examination and imaging examination until tumor progression. For patients with tumor progression, follow-up is performed by phone every 3 months until death. The following information should be collected as much as possible during follow-up: subsequent anti-tumor treatment and survival data. Patients with preoperative disease progression should withdraw from the study and enter into the follow-up stage as well.

**9.4 Discontinuation and withdrawal criteria**

The investigator has the right to discontinue the investigational drug treatment for a patient or withdraw a patient from the study at any time. In addition, patients have the right to request to discontinue the investigational drug or withdraw from the study at any time and for any reason. Reasons for discontinuation of the investigational drug or study withdrawal may include, but are not limited to, the following:

- Patients withdraw informed consent at any time.
- Presence of a medical event that, at the discretion of the investigator, can jeopardize the patient’s safety if the study is to continue.
- Early withdrawal from the study is considered by the investigator to be in the best interest of the patient.
- Patients do not follow the study protocol.

Every effort should be made to obtain information on patients withdrawn from the study. The primary reason for withdrawal from the study should be recorded on the CRF. After withdrawal of informed consent, patients should not be followed up for any reason. Patients who withdraw from the study should not be replaced by other patients.

**10. Statistical analysis**

**10.1 Study population**

The analysis population of this study includes full analysis set (FAS), per protocol set (PPS) and safety set (SS). The principle of **intention-to-treat (ITT) population** refers to the principle that the analysis is performed according to the original randomized intention, that is, the analysis should include all randomized subjects, and the subjects assigned to any treatment group should be followed up, evaluated and analyzed as members of this group, regardless of the actual treatment received.

**FAS** is defined as the set of data obtained after the least and fairest elimination of data from all subjects, which is as close as possible to the ideal according to the ITT principle.

**PPS** is a subset of FAS whose subjects are sufficiently compliant with the protocol and can be assessed for the effect of treatment and whose characteristics meet the following principles: (1) completion of predetermined treatment; (2) measurability of primary study endpoints; (3) absence of major protocol violations, including violations of the eligibility criteria. If the PP population reaches more than 95% of ITT population, the analysis of PP population is not necessary.

**SS** includes all patients who participate and receive at least one dose of the investigational drug, and if the participating population is not consistent with the as-treated population, the safety analysis population will be based on the as-treated population.

